### Strategies to improve adherence to interventions {11c}

Not applicable. ESPB or QLB is performed with a single injection on the day of the surgery. Our institution’s standard protocol for anesthesia and postoperative pain management is strictly followed, regardless of the study. There will be no difficulty with non-adherence.

### Relevant concomitant care permitted or prohibited during the trial {11d}

Not applicable: No relevant concomitant care or intervention will be permitted or prohibited during the trial.

### Provisions for post-trial care {30}

According to the provisions of the compensation agreement, the investigator compensates the subject for physical damage caused by the intervention in a clinical trial through compensation insurance. Insurance also covers matters not included in the compensation agreement in accordance with the relevant laws of the Republic of Korea and the institutional regulations of Samsung Medical Center.

### Outcomes {12}

The primary outcome is cumulative opioid consumption 24 h after surgery. Secondary outcomes include: cumulative opioid consumption in the PACU (admission, highest, and discharge), at 48 h, and 72 h after surgery; pain severity at rest and when coughing in the PACU (admission, highest, and discharge), at 24 h, 48 h, and 72 h after surgery; postoperative nausea or vomiting in the PACU, at 24 h, 48 h, and 72 h after surgery; quality of sleep on the first night; patient satisfaction with pain relief at 24 h after surgery; postoperative recovery quality at 24 h after surgery using the Korean version of the Quality of Recovery-15 scale (QoR-15 K) [11]; the incidence of procedure-related complications (hematoma, infection, or needle trauma); time to first flatus; and plasma ropivacaine concentrations at 30 min, 45 min, 60 min, and 240 min after the end of both administrations of local anesthetics.

### Participant timeline {13}

The schedule of enrollment, interventions, and assessments for the participants is shown in Figs. 1 and 2.

**Fig. 1 Fig1:**
[figure not shown]
Flowchart of trial. ESPB, erector spinae plane block; QLB, quadratus lumborum block

**Fig. 2 Fig2:**
[figure not shown]
Schedule of enrolment, interventions, and assessments. − t_1_, the eve of surgery; T0, after induction of general anesthesia; T1, PACU admission; T2, PACU discharge; T3, 24 h after surgery; T4, 48 h after surgery; T5, 72 h after surgery

### Sample size {14}

The sample size was calculated based on a previous study and the retrospective clinical data from our institution [5]. The mean cumulative opioid consumption during 24 h after laparoscopic liver resection was 45.5 mg with a standard deviation (SD) of 21.8 mg in IV morphine equivalent dose (MED) [12]. We hypothesized that bilateral ESPB and QLB will reduce cumulative opioid consumption by 30% compared with the control group. With an alpha of 0.05 and a beta of 0.8, 34 participants are required in each group using Dunnett’s test. Assuming a dropout rate of 10%, we plan to enroll 114 participants in the study. The sample size was calculated using the PASS 2021 (NCSS, LLC. Kaysville, UT, USA).

### Recruitment {15}

Patients will be informed in detail of the course of the study, all study procedures, potential risks, and the benefits of each intervention one day before surgery. The chief investigator is responsible for participant recruitment. After screening adult patients aged 19–69 years who undergoing liver resection during the clinical trial period at Samsung Medical Center, enrollment will be performed using a consecutive sampling method on the eve of the surgery.

## Assignment of interventions: allocation

### Sequence generation {16a}

Eligible participants will be randomly assigned to the control, ESPB, or QLB group in a 1:1:1 ratio. Randomly assigned sequences are generated using a web-based service (www.sealedenvelope.com) by an independent statistician with a fixed block size of six.

### Concealment mechanism {16b}

The allocation information will be sealed in an opaque envelope and piled up in a cabinet in the research office. Only the independent statistician has access to the randomization list and allocation concealment. Randomization information will be managed confidentially such that the list is not disclosed to the evaluator.

### Implementation {16c}

The independent anesthetic nurse will open the sealed envelope of allocation information to confirm the assignment information on the operation day and prepare local anesthetics accordingly.

## Assignment of interventions: blinding

### Who will be blinded {17a}

All participants will be blinded because ESPB or QLB will be performed after the induction of general anesthesia. A blinded independent outcome assessor will collect the postoperative outcome data. The attending medical staff in the PACU and caregivers in the surgical ward will be blinded to the group allocation. The data analyst will be blinded to group allocation.

### Procedure for unblinding if needed {17b}

In case of medical necessity or emergency related to the procedure, the chief investigator could decide to unblind and inform the patient and attending medical staff.

## Data collection and management

### Plans for assessment and collection of outcomes {18a}

All interventions and outcome assessments will be performed by a medical doctor. The blinded outcome assessor will visit the patient five times after surgery (time at PACU admission and discharge, at 24 h, 48 h, and 72 h after surgery) and examine the patient. Opioid consumption will be collected cumulatively at each time point and presented as IV MED. To minimize missing values, the infusion information of PCA is automatically collected in the device log and exported to an Excel file. Pain severity will be assessed at designated times using a numerical rating scale (NRS, 0–10; 0 = no pain, 10 = worst imaginable pain). Opioid-related side effects including nausea, vomiting, and pruritus will be examined during 72 h after surgery using a 4-point scale (0–3; 0 = none, 1 = mild, 2 = moderate, 3 = severe). Twenty-four hours after surgery, all participants will be requested to rate their sleep quality and satisfaction with postoperative pain relief using a Likert scale (1–5; 1 = very dissatisfied, 2 = somewhat dissatisfied, 3 = neutral, 4 = somewhat satisfied, 5 = very satisfied). The QoR-15 K questionnaire will be measured preoperatively and 24 h postoperatively to assess the quality of postoperative recovery.

### Plans to promote participant retention and complete follow-up {18b}

Maximum effort will be made to engage participants in all assessments whenever possible and achieve high adherence in this study. The appointments for follow-up assessments will be provided to the participants in advance. The research team will conduct an assessment of the participants with careful consideration of their individual status.

### Data management {19}

Data will be recorded on a paper-based Case Report Form (CRF) and converted to an electronic CRF. The paper CRF will be locked into the storage of the research office. At least two members of the research team will prepare the electronic CRF, and the CRF will be checked for consistency every 20 enrollments.

### Confidentiality {27}

Personal data will be anonymized and identified using a predetermined numeric code in a randomization list. A link to personal data, including name and contact number, will be recorded in the subject identification log. The subject identification log will be stored in a separate locked storage in the research office.

### Plans for collection, laboratory evaluation, and storage of biological specimens for genetic or molecular analysis in this trial/future use {33}

Not applicable. We will perform blood sampling to measure plasma ropivacaine concentration. However, the blood samples will be anonymized prior to analysis, and no genetic or molecular analyses are planned in this study. The samples will be discarded immediately after analysis.

## Statistical methods

### Statistical methods for primary and secondary outcomes {20a}

After assessing normality, continuous variables will be presented as mean ± standard deviation or median with an interquartile range. Categorical variables will be presented as numbers (%).

The primary outcome, cumulative opioid consumption 24 h after surgery, will be compared using Dunnett's test. For continuous variables of the secondary outcomes, descriptive statistics for each group will be presented, and the mean difference among the groups will be confirmed using one-way analysis of variance (ANOVA). If the assumption of normality is not satisfied, the median difference among the groups will be analyzed using the Kruskal–Wallis test. For plasma ropivacaine concentration, the peak plasma ropivacaine concentration (Cmax) and time to Cmax (Tmax) will be compared using an independent two-sample *t*-test or Wilcoxon rank-sum test, depending on normality testing. For categorical variables, the difference in the ratio among the three groups will be confirmed using the chi-square test or Fisher’s exact test. Statistical significance shall be set at a two-sided *P* < 0.05. The analysis will be performed using SPSS, Version 27.0 (IBM Corp, Armonk, NY, USA).

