## Interventions

### Explanation for the choice of comparators {6b}

The participants in the control group will be managed according to an institutional protocol.

The standardized anesthesia protocol is as follows: No premedication is given to any of the participants. Patient monitoring, including non-invasive blood pressure, EKG, pulse oximetry, and bispectral index (BIS), will be applied. After preoxygenation, general anesthesia will be induced with an IV injection of propofol (2 mg/kg) and rocuronium (0.8 mg/kg). After tracheal intubation, an arterial catheter is placed in the radial artery to continuously monitor blood pressure. Anesthesia is maintained with sevoflurane and IV infusion of remifentanil. The anesthetic concentration is adjusted to target BIS values of 40–50 and mean blood pressure and heart rate within 20% of the pre-induction values. IV hydromorphone (0.01 mg/kg) is injected 20 min before the end of surgery.

The standardized postoperative pain management protocol is as follows. After confirming full awakening from anesthesia, intravenous (IV) patient-controlled analgesia (PCA) is administered to the patient in the post-anesthesia care unit (PACU). The IV PCA consisting of fentanyl is programmed with a basal flow rate of 0.1 mL/h, bolus of 1 mL (15 μg), and a 15-min lockout interval. IV PCA is continued until postoperative day 3. In the ward, all patients are regularly administered IV ibuprofen 800 mg every 8 h. If patients present with breakthrough pain (NRS ≥ 4/10), IV hydromorphone (2 mg) is administered. Postoperative nausea and vomiting are treated with IV metoclopramide (10 mg).

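### The primary Dunnett comparison is valid but uses no baseline covariate; prespecified adjustment is a cheap change that may gain precision, by an amount the documents do not allow one to fix

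*Protocol article*

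**What the plan says.** All references are to the protocol article.

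- **Primary test, section {20a}.** Cumulative opioid consumption at 24 h "will be compared using Dunnett" (Dunnett's test). No covariate is named. The pairwise t or Wilcoxon tests of the same outcome in section {20b} name none either.
- **Randomisation, section {16a}.** The sequence is generated 1:1:1 "with a fixed block size of six". No stratification factor is given.
- **Baseline information.** Section {18a} states that the QoR-15 K "questionnaire will be measured preoperatively and" again at 24 h. Age appears as an eligibility limit of 19–69 years in section {10}. Weight is implied by the mg/kg anaesthetic doses in section {6b}. The article does not say that age or weight is entered as trial data.
- **Sizing, section {14}.** "With an alpha of 0.05 and a beta of 0.8, 34 participants are required in each group", using Dunnett's test. The article does not say whether the 0.8 refers to each comparison, to at least one, or to both.

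**The concern.** Neither the design nor the primary analysis, as written, uses prognostic information. Planned opioid consumption varies widely: the SD is 21.8 mg on a mean of 45.5 mg, a coefficient of variation of 21.8/45.5 = 48%. Whatever part of that spread is predictable from values known before surgery stays in the error term of an unadjusted comparison. A prespecified adjusted model would remove it without recruiting anyone. It would also take account of chance differences between arms in those variables, which can be noticeable with about 34 patients per arm.

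At stake is the width of the two confidence intervals against control and the power for each. Power matters here because the hypothesis concerns each block against control.

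**Working it through.** **Inputs**

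- Control values, section {14}: "The mean cumulative opioid consumption during 24 h after laparoscopic liver resection was 45.5 mg with a standard deviation (SD) of 21.8 mg".
- Effect, section {14}: each block "will reduce cumulative opioid consumption by 30% compared with the control group". The difference is 0.30 × 45.5 = 13.65 mg, or 13.65/21.8 = 0.626 SD, taken as equal for both blocks.
- Level, section {20a}: "Statistical significance shall be set at a two-sided" 0.05.
- The 0.8 that section {14} labels beta is read as power of 0.80.
- R², the share of variance in 24 h consumption explained by age, weight and preoperative QoR-15 K, is **not in the documents**. A range is shown.

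**Step 1. Reproduce the stated sample size.** With three arms and pooled variance, df = 3 × (34 − 1) = 99, and the simulated two-sided Dunnett critical value is about 2.245. The noncentrality of each contrast is 13.65 / (21.8 × √(2/34)) = 0.626 × √17 = 2.58. Simulation gives:

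| Evaluable per group | Each block | At least one | Both |
|---|---|---|---|
| 34 | 63% | 79% | 48% |
| 35 | 65% | 80% | 50% |
| 38 | 69% | 83% | 54% |
| 49 | 81% | 92% | 70% |

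So 34 per group matches power of 80% for at least one contrast, to within one patient. Per-block power of 80% needs about 49. The dropout step also reproduces: 34/0.9 = 37.8, rounded up to 38, and 3 × 38 = 114.

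**Step 2. Add covariates.** The residual SD becomes 21.8 × √(1 − R²), and the noncentrality becomes 2.58/√(1 − R²). Losing three of 99 df is ignored as negligible. At 34 per group:

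| Assumed R² | Residual SD (mg) | Noncentrality | Each block | At least one |
|---|---|---|---|---|
| 0 | 21.8 | 2.58 | 63% | 79% |
| 0.05 | 21.2 | 2.65 | 66% | 81% |
| 0.10 | 20.7 | 2.72 | 68% | 83% |
| 0.15 | 20.1 | 2.80 | 71% | 85% |
| 0.20 | 19.5 | 2.89 | 74% | 87% |
| 0.30 | 18.2 | 3.09 | 80% | 91% |

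With no dropout (38 per group), per-block power runs from 69% at R² = 0 to 71% at 0.05 and 79% at 0.20.

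**Step 3. Cross-check.** Adjustment acts like multiplying the sample by 1/(1 − R²). At R² = 0.30, 34/0.70 = 48.6, which agrees with the 49 per group in step 1. Confidence intervals shrink by 1 − √(1 − R²): 2.5% at R² = 0.05 and 10.6% at 0.20.

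**The case against.** The strongest reply is that nothing here is wrong. A Dunnett test after blocked 1:1:1 randomisation controls the type I error for the two comparisons with control, and it is the method used for sizing. That stands. Four stronger readings are tempting, and the documents support none of them.

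- **That the unadjusted estimate is biased.** Randomisation prevents bias over repeated trials, and the unadjusted standard error already includes chance imbalance. Imbalance matters only so far as the covariate is prognostic.
- **That all three covariates are already recorded.** This is stated only for the QoR-15 K. Age and weight are inferred from eligibility and dosing.
- **That precision is certainly lost.** No correlation with 24 h consumption is given for any of the three. Section {6b} gives the PCA bolus and rescue analgesic in fixed amounts, and section {11a} does the same for the ropivacaine. Exposure per kg therefore varies, which is a reason weight might matter, but not evidence that it does.
- **That the 63% results from not adjusting.** It results from a sample size that corresponds to power for at least one contrast. Adjustment at R² of 0.05 to 0.20 eases it without curing it.

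Two practical objections carry some weight. Section {20c} expects an almost complete primary outcome and does not replace missing data, so a questionnaire covariate could drop patients whose outcome is known. Also, the tabulated Dunnett value is only approximate with unequal groups or covariates. Both can be met in one clause.

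Finally, an analysis plan that is not shown may provide for adjustment. The point therefore rests on the primary method the article does state, and not on missing detail.

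**Conclusion.** The point holds as a cheap improvement. The primary analysis is sound but makes no use of baseline information that the trial measures or must know, so precision may be lost.

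At 34 evaluable per group, and if R² lies between 0.05 and 0.20, adjustment would add about 2 to 11 percentage points of power per block (63% to 66–74%) and about 2 to 8 points for at least one block (79% to 81–87%). The assumptions are the planning mean and SD, an equal 30% reduction with both blocks, a two-sided Dunnett test at 0.05, and an R² that the documents do not supply. If R² is near zero the gain is near zero and the cost is negligible. Per-block power of 80% at 34 per group would need R² of about 0.30, so adjustment should not be presented as a remedy for the sample size.

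**What to change.** In section {20a}, before unblinding, prespecify the primary analysis as a linear model of 24 h consumption (IV MED) on group, age, body weight and preoperative QoR-15 K total. Report the ESPB–control and QLB–control contrasts with Dunnett adjustment for two comparisons, taking the critical value (about 2.24) from the model's degrees of freedom. State that age and weight are recorded as baseline data.

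Add that a patient with a missing baseline covariate stays in the analysis by simple baseline imputation, such as the mean over all arms. Limit the no-replacement sentence in section {20c} accordingly, so that the two sections agree. Keep the unadjusted Dunnett test as a sensitivity analysis.

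The cost is a few sentences of text, three degrees of freedom (99 to 96 at 34 per group), and a general linear model in the SPSS already planned, with the Dunnett critical value applied to the adjusted contrasts by hand. No further patients or visits are needed.

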### Methods for additional analyses (e.g., subgroup analyses) {20b}

Subgroup analyses will be performed for pairwise comparison. We will compare the primary outcome, cumulative opioid consumption at 24 h after surgery, between the two groups in each pair using an independent two-sample *t*-test or Wilcoxon rank-sum test as appropriate. Multiple comparisons for subgroup analysis will be adjusted using Bonferroni correction. One-way analysis of variance (ANOVA) with Tukey’s test will be used to perform pairwise comparisons for other outcomes. If the data do not satisfy normality, the Kruskal–Wallis test and Dunn’s method will be used to perform multiple comparisons.

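### The preoperative QoR-15K score is collected but not used in the stated comparison of 24 h scores, which gives up some precision on this secondary outcome

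*Protocol article*

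**What the plan says.** Under Outcomes {12}, the secondary outcome is "postoperative recovery quality at 24 h after surgery using the Korean version of the Quality of Recovery-15 scale". It is the 24 h score, not a change from baseline.

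Under Plans for assessment and collection of outcomes {18a}, the scale is taken twice: "The QoR-15 K questionnaire will be measured preoperatively and 24 h postoperatively to assess the quality of postoperative recovery".

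Under Statistical methods for primary and secondary outcomes {20a}, the rule for continuous secondary outcomes is that "the mean difference among the groups will be confirmed using one-way analysis of variance (ANOVA"). If normality fails, "the median difference among the groups will be analyzed using the Kruskal–Wallis test". Peak ropivacaine concentration and its timing have their own two-group tests and fall outside this rule.

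Under Methods for additional analyses {20b}, ANOVA with Tukey's test "will be used to perform pairwise comparisons for other outcomes", with Kruskal–Wallis and Dunn's method as the non-normal alternative.

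No section mentions a covariate, an analysis of covariance or a change score for QoR-15K.

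**The concern.** The protocol collects a baseline for the same scale in the same people, and then names tests that cannot take it into account. People who feel well before surgery may tend to score higher at 24 h whichever group they are in. To the extent that they do, this between-person variation stays in the residual of a one-way ANOVA and widens every interval.

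The sample size was set on opioid consumption alone, so the precision of the QoR-15K comparison depends entirely on how it is analysed. QoR-15K is also the outcome that addresses the stated aim of comparing postoperative recovery profiles most directly. This is more than a detail left to a later analysis plan: the protocol names the test, the fallback and the pairwise procedures, so a later plan that used ANCOVA would depart from the stated method.

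**Working it through.** **Inputs from the document.** Three groups, 1:1:1, 34 evaluable per group (38 enrolled), two-sided 5% level, one-way ANOVA on the 24 h score.

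**Input assumed.** The correlation r between the preoperative and 24 h QoR-15K scores. The document gives no value, so a range is shown.

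**The plan's own figure.** There is none for QoR-15K. The only sample-size figure concerns the primary outcome: "With an alpha of 0.05 and a beta of 0.8, 34 participants are required in each group". The stated beta of 0.8 is read here as power of 0.80.
- The effect is 0.30 × 45.5 = 13.65 mg, and 13.65 / 21.8 = 0.626 SD.
- With this reduction in both block groups, simulated two-sided Dunnett power for at least one significant comparison is 0.787 at 34 per group, 0.798 at 35 and 0.81 at 36. The stated 34 is thus reproduced closely.
- For dropout, 34 / 0.9 = 37.8, rounded up to 38, and 3 × 38 = 114.

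This fixes n = 34 for the check below and has no other bearing on the point.

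**Step 1: variance ratio.** Adjusting for one baseline covariate multiplies the variance of a group difference by about

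(1 − r²) × [1 + 1/(3n − 5)].

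The second factor is the price of estimating the slope. With n = 34 it is 1 + 1/97 = 1.0103. Example at r = 0.5: 0.75 × 1.0103 = 0.758.

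**Step 2: equivalent sample size.** The unadjusted n per group giving the same precision is 34 divided by the ratio. Example at r = 0.5: 34 / 0.758 = 44.9.

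**Step 3: power for illustration.** Assume a benefit of 0.5 SD in both block groups. The group means are 0, 0.5 and 0.5 with overall mean 1/3, so the squared deviations sum to 1/9 + 1/36 + 1/36 = 1/6. The noncentrality is 34 / 6 = 5.67 unadjusted, and 5.67 divided by the ratio with ANCOVA. Omnibus power comes from the noncentral F distribution.

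| Assumed r | Variance ratio, ANCOVA to ANOVA | Equivalent unadjusted n per group | Omnibus power (0.545 unadjusted) |
|---|---|---|---|
| 0.1 | 1.00 | 34.0 | 0.544 |
| 0.2 | 0.97 | 35.1 | 0.558 |
| 0.3 | 0.92 | 37.0 | 0.582 |
| 0.4 | 0.85 | 40.1 | 0.619 |
| 0.5 | 0.76 | 44.9 | 0.672 |
| 0.6 | 0.65 | 52.6 | 0.745 |
| 0.7 | 0.52 | 66.0 | 0.841 |

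**Step 4: break-even.** The ratio equals 1 when 1 − r² = 97/98, that is r² = 1/98 and r ≈ 0.10. Below that, adjustment loses at most about 1% in variance (1.0103 at r = 0).

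**Step 5: missing baselines.** Ignoring the small change in the slope term, a complete-case ANCOVA matches the unadjusted test on 34 per group when the number with both scores is 34 × ratio: 34 × 0.97 = 33.0 at r = 0.2, 34 × 0.919 = 31.2 at r = 0.3, and 34 × 0.758 = 25.8 at r = 0.5. At a low r, losing one to three people per group for want of a preoperative score would use up the gain. At r = 0.5 it would take about eight.

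**Step 6: change score.** Subtracting the baseline gives a variance ratio of 2(1 − r): 1.4 at r = 0.3, 1.0 at r = 0.5 and 0.6 at r = 0.7. It is worse than the plain 24 h score when r is below 0.5, so it does not replace ANCOVA.

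**The case against.** The strongest case on the other side is that nothing here is wrong. Under 1:1:1 randomisation, comparing 24 h scores without adjustment is unbiased and controls the type I error, and the standard error already allows for chance imbalance at baseline. The test matches the outcome as defined. Only one item in a long secondary list is affected. The gain rests on an unknown r: a score taken before major surgery may predict the 24 h score weakly, and at r of 0.2 or less the gain is negligible. All of this stands. It limits the size of the point but does not remove it, because adjustment costs almost nothing when r is small and helps when r is moderate.

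Some stronger readings are tempting but unsupported:
- *The baseline is discarded.* The document does not say so. The score may still be reported descriptively; it is only absent from the stated between-group test.
- *Adjustment is free.* It spends one degree of freedom. Since the protocol does not fill in missing values, anyone without a preoperative score would also leave a complete-case ANCOVA.
- *The Kruskal–Wallis fallback is an error.* It is a valid pre-specified test. It shares the limitation that it ignores the baseline, but no fault in it has been shown.
- *All continuous secondary outcomes are affected.* The point concerns QoR-15K, the scale that the protocol says is measured before surgery. The ropivacaine summaries are tested separately.

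**Conclusion.** The point holds as one of efficiency. The protocol fixes a comparison of 24 h QoR-15K that leaves out a baseline it already collects, and so accepts a less precise estimate than its own data allow. Validity, the primary outcome and the sample size are not in question.

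The size cannot be fixed from the document. It runs from no gain at r near 0.1, through about 8% less variance at r = 0.3 and 24% at r = 0.5, to 35% at r = 0.6. These figures assume 34 per group with both scores observed and a roughly linear relation between them. The power figures also assume a 0.5 SD benefit in both block groups, which is illustrative and not taken from the document. A reader should not conclude that the QoR-15K result would be misleading as planned; it would only be less precise than it could be.

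**What to change.** In Statistical methods for primary and secondary outcomes {20a}, add that the 24 h QoR-15K score will be analysed by ANCOVA with group as factor and the preoperative QoR-15K score as covariate. In Methods for additional analyses {20b}, except QoR-15K from the general ANOVA-and-Tukey rule, and state that the three adjusted pairwise mean differences will be reported with 95% confidence intervals and a named multiplicity adjustment. The existing rank-based test may stay as a sensitivity analysis if residuals are clearly non-normal.

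Report how many participants lack a preoperative score. If there are any, show the unadjusted comparison in everyone with a 24 h score beside the ANCOVA, so that the effect of dropping them is visible.

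The cost is a few sentences in two sections, made before the analyst sees results by group, and one degree of freedom in the analysis. No new data, visits or participants are needed.

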Therefore, in this study, we shall investigate the analgesic efficacy of ESPB or posterior QLB with 40 mL of 0.5% ropivacaine after laparoscopic liver resection compared with that in the control group. We will also measure chronological changes in plasma ropivacaine concentrations in both block groups to determine the safety of the local anesthetic dose in these patients. We hypothesize that ESPB or posterior QLB would reduce opioid consumption compared with conventional opioid-based analgesia in patients undergoing laparoscopic liver resection.

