### Objectives {7}

We aim to evaluate the analgesic efficacy of the two interfascial blocks of ESPB and QLB in patients undergoing laparoscopic liver resection by comparing cumulative opioid consumption 24 h after surgery. We will investigate the differences in pain severity, cumulative opioid consumption, opioid-related side effects, and any block-related adverse events within 72 h after surgery among the groups. Postoperative recovery profiles will be also compared between the groups.

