### Adverse event reporting and harms {22}

The chief investigator will report any serious adverse events to each institutional review board within seven days of the notice. Mild adverse events and harm will be reported within 15 days of notice. When reporting adverse events or harm, we shall equally report causalities, time of occurrence, severity, seriousness, provided management, and the relationship with the present clinical trial.

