Our study has several limitations. First, the sham procedure is not used for participants in the control group. Second, the optimal dose of ropivacaine for ESPB or QLB has not been determined. Because ropivacaine is mainly eliminated by hepatic metabolism, delayed ropivacaine clearance in patients with liver disease may increase the risk of local anesthetic systemic toxicity (LAST), which may be aggravated after liver resection [26]. Based on our previous study [10], the peak plasma concentrations of ropivacaine were approximately 3-fold below the threshold for systemic toxicity after administration of 40 mL of 0.375% ropivacaine. Therefore, the 40 mL of 0.5% ropivacaine (approximately 15% increased dose) used in this study is not expected to reach the systemic toxicity threshold. Third, to ensure safety, only 20 participants from each block group will be tested for plasma ropivacaine concentration. The sample size of 20 may be too small to discriminate LAST between the groups. Fourth, we plan to measure total plasma ropivacaine concentrations. However, ropivacaine toxicity is dependent on unbound ropivacaine clearance, and the total plasma ropivacaine concentration alone may not be sufficient to determine systemic toxicity [27].

In summary, we anticipate that this trial will provide evidence for the efficacy and safety of ESPB and posterior QLB in patients undergoing laparoscopic liver resection. In addition, our data will provide clinical implications for determining the optimal dose of ropivacaine for ESPB and posterior QLB.

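### The planned ESPB-versus-QLB test of Cmax and Tmax fits the between-block aim but not the dose-safety aim, which needs a count of patients above a stated toxicity threshold

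*Protocol article*

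**What the plan says.** **Aim.** Background and rationale {6a} says concentrations are followed over time in both block groups "to determine the safety of the local anesthetic dose in these patients". The Abstract (Methods) gives a second aim: to investigate whether concentrations differ between ESPB and QLB.

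**Data.** Outcomes {12} lists "plasma ropivacaine concentrations at 30 min, 45 min, 60 min, and 240 min after the end of both administrations". Sections {26b} and {11a} limit sampling to 20 patients per block group. Both block groups receive the same volume and concentration of ropivacaine.

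**Analysis.** In section {20a}, "the peak plasma ropivacaine concentration (Cmax) and time to Cmax (Tmax) will be compared using an independent two-sample" t-test or a Wilcoxon rank-sum test, chosen by normality testing. For continuous secondary outcomes generally, "descriptive statistics for each group will be presented", in the form of mean with SD or median with quartiles.

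**Clinical toxicity.** Outcomes {12} includes "the incidence of procedure-related complications (hematoma, infection, or needle trauma". Objectives {7} is wider: "any block-related adverse events within 72 h after surgery among the groups". Section {22} adds general reporting: "The chief investigator will report any serious adverse events to each institutional review board within seven days of the notice".

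**Benchmark.** The Discussion judges safety by peaks relative to a systemic toxicity threshold, which earlier peaks were about 3-fold below. It gives no numeric value. It closes by saying that "our data will provide clinical implications for determining the optimal dose of ropivacaine for ESPB and posterior QLB".

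**The concern.** Whether a dose is safe is a question about absolute levels in individuals, and about clinical toxicity events. The Discussion treats it that way when it sets earlier peaks against a threshold. The inference in {20a} asks a different question: whether one block gives higher or later peaks than the other. A non-significant p-value there could easily be read as reassurance about the dose, although it carries no information on the level that the two blocks share.

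The Discussion also names systemic toxicity as the main worry with this drug after liver resection. Yet the list of complications in {12} covers only needle-related harm. The stake is a secondary safety conclusion, not the primary endpoint.

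**Working it through.** **1. What the between-block test can show.** Let T be the toxicity threshold and m the mean Cmax in each arm. If the blocks behave alike, the tested difference is m − m = 0 whatever the ratio m/T. The test behaves the same when both arms are well below T and when both are above it. T does not enter the test.

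**2. What the planned summaries can show.** With n = 20, about 0.25 × 20 = 5 patients lie above the upper quartile, and a median with quartiles does not say how far above. Mean with SD gives neither the maximum nor a count above T. So per-block levels will be visible, but the number of individuals above T will not.

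**3. What a threshold count could show.** The sub-study has no sample size calculation to reproduce. Inputs: 20 sampled patients per block, 40 in all ({26b}, {11a}). For 0 events in n, the two-sided exact 95% upper limit is 1 − 0.025^(1/n):

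- n = 20: 1 − 0.025^(1/20) = 0.168, or 16.8%.
- n = 40: 1 − 0.025^(1/40) = 0.088, or 8.8%.

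Even a clean result would leave a true exceedance rate of about 1 in 11 (1/0.088 = 11.4) compatible with the pooled data.

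**4. Why clinical toxicity should be counted in all block patients.** The planned block total is 2 × 114/3 = 76. With 0 of 76, the upper limit is 1 − 0.025^(1/76) = 4.7%. The documents give no event rate, so the rates below are assumptions. The chance of seeing at least one event is 1 − (1 − p)^n:

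| Assumed rate p | 40 sampled patients | 76 block patients |
|---|---|---|
| 0.1% | 3.9% | 7.3% |
| 1% | 33.1% | 53.4% |
| 2% | 55.4% | 78.5% |

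**5. The reassurance carried over from the earlier study.** The Discussion puts the dose increase at about 15%. The article's own figures give 40 mL × 5 mg/mL = 200 mg against 40 mL × 3.75 mg/mL = 150 mg, and 200/150 − 1 = 33.3%. If peaks scale with dose (an assumption), the 3-fold margin becomes 3/1.333 = 2.25-fold. With the stated 15% it would be 3/1.15 = 2.6-fold. These statements must be reconciled. Until they are, the prior margin is a weaker substitute for this trial's own threshold summary.

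**The case against.** The other side has several sound points.

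- **The test has a proper purpose.** The abstract's between-block aim is answered by a two-sample comparison. This stands, and the comparison should stay.
- **More than the test is planned.** A reader might infer that the Cmax and Tmax comparison is the only analysis, so that the safety aim goes wholly unanswered. The article does not support that. Section {20a} promises per-group descriptive statistics for continuous secondary outcomes, and {12} lists the timed concentrations among the secondary outcomes. The reported levels can be set informally against a benchmark.
- **Toxicity can be captured.** A reader might infer that a toxicity event could not be recorded. That is also unsupported: the Abstract, {7} and {22} cover block-related and general adverse events. What remains is narrower: toxicity is not a named, counted outcome.
- **Tmax.** It can take only four sampled values, which might suggest that a t-test would mislead. But {20a} already provides a rank test when normality fails, so nothing rests on this.
- **The limits reflect sample size.** The 16.8% and 8.8% would be the same under any analysis of 20 or 40 patients, and the Discussion admits that 20 is small and that total concentration may not settle toxicity. This is correct. The limits do not measure the mismatch; they show how far a safety statement could go. The admitted limitation on numbers is framed as discriminating toxicity between groups, so it does not cover the absolute question.
- **Optimal dose.** This is a closing remark, not an objective. It is secondary here, although a single dose per block cannot by itself locate an optimum.
- **Detail left to a fuller plan.** Interval methods and table layouts may well be elsewhere. The mismatch between the stated aim and the stated inference is in the article itself.

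**Conclusion.** The concern holds in a limited form. The stated inference answers the between-block question and not the dose-safety question, and the stated summaries do not show individual high peaks. This is worth correcting because safety is a declared reason for drawing the samples and the data needed are already being collected. It does not touch the primary outcome.

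The upper limits of 16.8% and 8.8% assume zero exceedances and complete sampling in 20 patients per block. They concern the highest concentration among four sampling times, so a peak before 30 min or between 60 and 240 min could be missed. They also concern total rather than unbound drug, a limit that the Discussion already acknowledges.

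**What to change.** 1. In {20a}, keep the Cmax and Tmax comparison and tie it to the between-block aim.
2. For the safety aim, state a numeric toxicity threshold with its source before the concentrations are analyzed. The Discussion refers to one without a value.
3. Report the number and proportion of sampled patients whose highest measured concentration exceeds it, per block and pooled, with exact 95% confidence intervals and the maximum observed.
4. In {12}, name local anesthetic systemic toxicity among the block-related outcomes and count it in every patient who received a block. State that denominator explicitly, because {11b} classes patients with inadequate spread or an unexpected serious adverse event as dropouts.
5. Word the safety conclusion to match the interval, and soften the closing remark on optimal dose.
6. Reconcile the stated size of the dose increase with the article's own concentrations.

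The cost is one case report form item, a little more analysis and a more cautious safety statement. No extra blood samples are needed.
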